### Consent process

The verbal consent process will be used to obtain consent for participation in the study as a result of the low literacy level of the FSWs. The interviewer will read the consent script to the participant. Once the consent is read, the participant will be given time to ask questions. The participant will verbally agree to participate, and the interviewer will sign the consent form indicating this verbal consent.

### Measurements

The primary outcomes of this study are determining the feasibility of working with brothel leadership in deploying condom use messages within brothels (measurement, the number of brothels consenting to the intervention); the attrition rate of FSWs residing within the brothels (measurement, the proportion of FSWs and brothels completing the intervention in the intervention monitoring database); and the adherence to intervention (measurement, number of sessions attended by each FSW). The secondary outcomes are to determine the feasibility of measuring the primary outcomes for the main trial (measurement, FSWs self-reported consistent condom use in the baseline and follow-up assessments) and enhancing self-efficacy in condom use negotiation with all clients and partners of FSWs (measurement, FSWs self-reported self-efficacy regarding the ability to negotiate condom use with different partner types in the baseline and follow-up assessments).

For the process outcomes, participants will be asked several questions at the end of the 16-week follow-up period using interviewer-administered semi-structured questionnaires. The process evaluation will measure the acceptability, suitability, content, and mode of delivery (measurement, self-reported adequacy of the duration, content, and delivery method of the intervention in the follow-up assessment).

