**Methods/design:**

The clusters in the randomized pilot trial will be brothels and female sex workers (FSWs) residing in the brothels will be the participants of the study. The participants will receive free condom distribution as well as HIV prevention messages on condom use and negotiation skills to increase self-efficacy in handling social and gender power plays within their environment. Twelve brothels will be randomized into experimental and control conditions with a minimum total sample size of 200 participants. Recruitment of participants will be carried out from within the brothels. The control condition will receive a standard intervention consisting of a minimum of six interactive sessions with peer educators (PE) engaging their peers through group discussions and one on one interaction using pre-designed HIV prevention messages. The experimental condition will receive the standard intervention as well as interactive sessions with the brothel leadership (chairladies and brothel managers) to facilitate consistent condom use and appropriate condom use policies, conditions, and messaging. Both interventions will be delivered over a maximum period of 16 weeks, and male and female condoms will be distributed during the intervention. Quantitative assessments will be carried out at baseline and at 16 weeks follow-up, and the pilot findings will inform feasibility of and sample size estimation for a phase III trial. The primary outcomes measured are recruitment rate attrition rate and adherence to the intervention. Consistent condom use outcomes by FSWs within the brothel with all partner types and enhanced self-efficacy for condom negotiation with all partner types will be the primary outcomes for the main study, and the feasibility of their measurement will be determined in this pilot trial.

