### Study design and setting

The study will be conducted in Abuja, Nigeria, and intervention components will be evaluated using a cluster randomized pilot trial approach, comparing a standard intervention (i.e., usual care) to a standard intervention in combination with the brothel leadership intervention. Randomization of the study participants at the brothel level will be carried out to limit contamination between the two intervention groups.

Clusters will be brothels with a minimum of five FSWs and presence of FSWs aged from 15–24 years of age. The criteria for inclusion into the study include females who undertake sexual activities with men in return for money or benefits, who reside in brothels, who provide verbal informed consent, as well as brothels with chairladies who provide consent for the study.

The structure of the study, key messages, monitoring tools, and training slides were developed with information obtained from the formative studies and several meetings with the HIV prevention specialists. The messages and interactions for the intervention will focus on improving consistent condom use and condom negotiation self-efficacy of FSWs residing in brothels. The training of the brothel leaders will be carried out prior to the intervention, and peer educators from the pool of trained peer educators within the existing SHiPs for MARPs project will be used. The activities for both the standard and the brothel leadership intervention groups will be implemented for 16 weeks and will include interactive sessions with the peer educators engaging their peers through group discussions and/or one on one interaction using pre-designed HIV prevention messages. Male and female condoms will be distributed for free during the intervention period. Various studies have shown that the FSW population is a migrant population with high mobility [15, 16], and this poses a challenge during implementation for this target group. To minimize this and facilitate follow-up of the girls within the intervention, the intervention will be carried out for 16 weeks and messages will be reinforced using information and communication materials (i.e., posters and leaflets with condom use messages).

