### Sample size

Based on recent experience in local brothels, we anticipate that there will be between 5 and 50 FSWs in each brothel. Since this is a pilot study with the aim of providing information on the feasibility, attrition rates, and sample size estimates for a larger pilot trial, we aim to recruit 12 brothels. The formula provided by Viechtbauer et al. [17] for the calculation of sample size required for a pilot was applied in the determination of the sample size using a confidence interval of 95% and a 5% probability of existence of a problem. This resulted in a required sample size of 59 to enable the detection of feasibility problems. Due to the high attrition rate often reported in studies with FSWs and the lack of previous knowledge regarding clustering in brothels, it is unlikely that we will have all the recruited participants at follow-up; thus, we aim to recruit 200 participants to account for both aspects.

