## Discussion

This paper presents the protocol that describes a pilot study to assess the feasibility and potential effect of an intervention aimed at increasing consistent condom use and improving condom negotiation skills of BB FSWs in Abuja, Nigeria. Should the current study demonstrate feasibility, outcomes will be used to design and inform a phase III pilot cluster randomized control trial (CRCT). The aim of the phase III pilot will be to further test the effectiveness of the behavioral intervention in improving consistent use of condoms by BB FSWs in Nigeria.

The mobility of sex workers is one of the challenges faced when programming for this target group [16]. To minimize this, the intervention is designed such that the core messages and activities are delivered within a short time span, thereby enabling most of the FSWs to benefit from it before they may need to change their location.

Formative research was conducted in collaboration with the target group and the brothel leaderships for the development of the interventions; this identified important issues for the development and relevance of the intervention. Involving the brothel leaderships in the development process initially led to some resistance due to their perceived notion that the FSWs will become distracted and that they will lose the girls within their brothels. Assurance of the benefits of the intervention on the health of the FSWs and the reputation of the brothel establishment as a whole was provided. The brothel leaders were enthusiastic about the intervention and provided the needed support, without which, it will be impossible to implement the intervention.

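### Leadership feasibility is measured by a count of consenting brothels, and no primary measure specifically shows whether leaders delivered their component

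*Protocol article*

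**What the plan says.** All references are to the protocol article.

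- **Measurements** lists three primary outcomes. The first is "determining the feasibility of working with brothel leadership in deploying condom use messages within brothels", measured by "the number of brothels consenting to the intervention". The second is attrition, measured as the proportion of women and of brothels completing the intervention according to the monitoring database. The third is adherence, measured as the number of sessions each woman attended. A process evaluation at 16 weeks adds participants' views on duration, content and delivery.
- **Study design and setting** puts among the inclusion criteria "brothels with chairladies who provide consent for the study".
- **Sample size** states "we aim to recruit 12 brothels", and the abstract states "Twelve brothels will be randomized into experimental and control conditions with a minimum total sample size of 200 participants".
- The **abstract** describes the primary outcomes differently: "The primary outcomes measured are recruitment rate attrition rate and adherence to the intervention". **Statistical analysis and data management** also mentions recruitment rates of brothels and participants, but ties them to the intervention arm and gives no denominator.
- **Allocation strategy** places randomization after baseline data collection.
- **Standard intervention** gives both arms at least six peer sessions. **Brothel leadership intervention** adds, in the experimental arm only, a one-day leader workshop, a refresher after 8 weeks, at least six group sessions for which the leader is responsible, and brothel rules on condom use.
- **Discussion** makes the next step conditional: "Should the current study demonstrate feasibility, outcomes will be used to design and inform a phase III pilot".

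**The concern.** The construct is what leaders do during 16 weeks, while the measure is what brothels agree to at entry. Because agreement is also required for entry, the count says little about recruitment and nothing about delivery.

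The leadership component is the only planned difference between the arms, and the pilot exists to find out whether it can be run. If its delivery is not measured, the investigators could carry into phase III planning an effect size and an intra-cluster correlation from brothels where the component was barely delivered. They could not then tell a weak intervention from an undelivered one.

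**Working it through.** **1. The plan's own figure.** Sample size uses 95% confidence and a 5% problem probability. n = ln(1 − 0.95) / ln(1 − 0.05) = 58.40, rounded up to 59. Check: 1 − 0.95^59 = 0.9515 and 1 − 0.95^58 = 0.9490. The stated 59 is reproduced, and nothing below changes it or the target of 200.

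**2. What values the consent count can take.** Inputs: consent is required for inclusion (Study design and setting) and the target is 12 (abstract; Sample size). Every included brothel is a consenter, so the count equals the number enrolled. It is at most 12 and equals 12 once the target is met. It falls below 12 only if recruitment falls short.

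**3. What the missing denominator hides.** The article does not give the number of brothels approached, so the values below are assumptions. With 12 consenting (exact Clopper-Pearson intervals):

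| Approached (assumed) | Consent proportion | 95% interval | Count reported |
|---|---|---|---|
| 12 | 100% | 73.5 to 100% | 12 |
| 15 | 80% | 51.9 to 95.7% | 12 |
| 20 | 60% | 36.1 to 80.9% | 12 |
| 30 | 40% | 22.7 to 59.4% | 12 |
| 40 | 30% | 16.6 to 46.5% | 12 |

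The count does not separate easy from hard recruitment.

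**4. Whether the recruitment rate elsewhere fills the gap.** The abstract names a rate and Measurements a number. The analysis section speaks of rates but attaches them to the intervention arm. A brothel that refuses is never randomized and belongs to no arm, so a brothel-level recruitment rate within one arm, taken literally, is 100% by construction. No section names brothels approached as the denominator.

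**5. Whether another primary outcome captures leader delivery.**

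- *Sessions attended per woman.* Experimental brothels have two streams of sessions: at least six by peer educators and at least six under the leader. The measure is one number per woman and is not said to be split. Six peer sessions plus no leader sessions gives 6, and so does three plus three.
- *Completion by women and brothels.* This may include leader sessions in the experimental arm, but the article does not say so.
- *Process evaluation.* This is not a primary outcome, and it records participants' opinions rather than sessions held.

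**6. Which brothels are counted.** No consent step after allocation is described. The count therefore pools control brothels, where leaders have no component to deliver, with experimental ones.

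**The case against.** The strongest reply is that the consent count is one of three primary outcomes. Low brothel completion or low attendance would show that the intervention is not workable, and completion is measured at brothel level. Since the experimental intervention includes the leader component, completing it plausibly includes leader sessions. A recruitment rate is named twice, and a rate implies a denominator. Operational definitions and progression thresholds are commonly left to the full protocol. Finally, the inclusion criterion concerns consent for the study, whereas the outcome concerns consent to the intervention, which could be a separate, later step.

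Much of this stands. A reader might infer that the count must be 12 whatever happens. It need not be: 12 is a target, the Discussion reports some initial resistance from leaders, and a shortfall would itself be a warning. A reader might also infer that the pilot cannot show infeasibility, or would be declared feasible even if no leader held a session. The article does not support that either, because two other primary outcomes can come out badly and the Discussion does not tie the phase III decision to the consent count alone.

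The reply does not remove the mismatch. The article does define a measure for leadership feasibility, and that measure is consent; this is a stated choice rather than an omitted detail. The number and the rate disagree between sections. No later consent step is described, and even if one existed, consent would still not be delivery.

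**Conclusion.** The point holds for this measure, not for the pilot's feasibility assessment as a whole. As worded, the first primary outcome is capped at 12, has no denominator and records entry rather than delivery. The remaining primary outcomes can show general infeasibility, but none is stated to isolate the leadership component.

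On size: a reported count of 12 is compatible with consent proportions from 100% down to 30% over the assumed range of 12 to 40 brothels approached, and it carries no information on leader sessions held. The conclusion assumes that consent to the intervention is the same entry step as the chairlady's consent for the study, since no other step is described. It also assumes that completion and attendance are recorded without separating leader-led from peer-led sessions, since no separation is stated. If the full protocol makes that separation, what remains is the choice of headline measure and the disagreement between number and rate.

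**What to change.** 1. Report recruitment as brothels consenting out of eligible brothels approached, across both arms and before randomization. Use this one definition in the abstract, Measurements and the analysis section, and drop the restriction to the intervention arm for this quantity.
2. Measure leadership feasibility by delivery. For each experimental brothel, record leader attendance at the workshop and at the refresher, and the number of leader group sessions held against the minimum of six already in Brothel leadership intervention. Record who led each session, so that leader and peer-educator sessions can be told apart.
3. State that these delivery results will be considered in the phase III decision. Any numeric cut-off is for the investigators to set.

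The cost is a screening log and a few added entries in the monitoring database the article already plans to use. The drawback is that the feasibility result may look less favourable than a count of consenting brothels.

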### Statistical analysis and data management

The overall recruitment and attrition rates of the brothels and participants for the intervention arm will be described. The Intra Cluster Correlation (ICC) and the effect size will be generated in addition to the attrition rates to enable sample size estimation required for a phase III trial.

As the FSWs are nested in brothels, we will use a multilevel regression approach with three levels to assess the potential effects and viability of the intervention on condom use behavior. The first level consists of the repeated measures within the participants (baseline and follow-up measurements), the second level are the FSWs, and the third level are the brothels, where the FSWs are nested. Multilevel logistic regression will be used to analyze the effects on condom use separately for steady partners and clients. The multilevel regression analysis was chosen because this allows for data missing at random, which is less strict than the requirement of data missing completely at random [18]. Each interviewed participant will be given a code, and the questionnaires and data sets will be stored in a password-protected computer and only researchers will have access to the data.

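### Attrition, a primary outcome meant to size phase III, is measured as completing the intervention rather than as a missing 16-week assessment

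*Protocol article*

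**What the plan says.** All references are to the protocol article.

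- **Measurements** names three primary outcomes: feasibility, attrition and adherence. Attrition is measured as "the proportion of FSWs and brothels completing the intervention in the intervention monitoring database". Adherence is a separate outcome, counted as the sessions each woman attends.
- **Statistical analysis and data management** states the use: "The Intra Cluster Correlation (ICC) and the effect size will be generated in addition to the attrition rates to enable sample size estimation" for phase III. The same section says "The overall recruitment and attrition rates of the brothels and participants for the intervention arm will be described".
- **Measurements** gives the data source for the condom-use outcome of the main trial: "FSWs self-reported consistent condom use in the baseline and follow-up assessments". Self-efficacy for negotiating condom use comes from the same two assessments. The **Abstract** fixes their timing: "Quantitative assessments will be carried out at baseline and at 16 weeks follow-up".
- **Sample size** raises the recruitment target because of high attrition, and explains that "it is unlikely that we will have all the recruited participants at follow-up".

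No section defines attrition by the follow-up assessment, and none says what a woman or a brothel must do to count as completing.

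**The concern.** A sample size is inflated for participants who will not contribute the outcome. Here the outcome is what a woman reports at the 16-week interview, so the relevant loss is a missing interview. Completing an intervention is a different event, and the article takes it from a different source, the monitoring database.

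The article uses one word for both. Its Sample size section treats attrition as recruited women not being there at follow-up, while its Measurements section gives the same word a measure based on completing the intervention.

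Informing the phase III sample size is a stated purpose of the pilot, and attrition is one of the three figures to be carried forward, with the ICC and the effect size. If the Measurements definition is followed as written, the figure carried forward describes receipt of the programme and not availability of the outcome.

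**Working it through.** **1. The plan's own figure.** The pilot size of 59 uses 95% confidence and a 5% problem probability:

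n = ln(1 − 0.95) / ln(1 − 0.05) = 58.40, rounded up to 59.

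This reproduces, and the point here does not touch it. The step from 59 to 200 is a factor of 200/59 = 3.39, which is said to cover attrition and clustering together. No split is given, so no anticipated attrition rate can be recovered from it.

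**2. The two quantities side by side.**

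| | Measure stated | Quantity needed for phase III |
|---|---|---|
| Event | Not completing the intervention | No 16-week assessment |
| Source | Intervention monitoring database | Baseline and follow-up assessments |
| Where in the article | Measurements | Sample size (its use of the word); Abstract and Measurements (source of the main-trial outcome) |

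**3. What a gap between them would do.** Let d_c be the proportion not completing, d_f the proportion missing at 16 weeks, and n the evaluable number required. Inflating by d_c enrols n/(1 − d_c) women and leaves n(1 − d_f)/(1 − d_c) evaluable. The correct enrolment is n/(1 − d_f). The article gives neither rate and no phase III number, so every input below is assumed. With n = 400 evaluable women:

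| d_c | d_f | Enrolled using d_c | Enrolment needed | Evaluable |
|---|---|---|---|---|
| 20% | 10% | 500 | 445 | 450 |
| 20% | 20% | 500 | 500 | 400 |
| 20% | 30% | 500 | 572 | 350 |
| 20% | 40% | 500 | 667 | 300 |
| 40% | 20% | 667 | 500 | 534 |
| 40% | 40% | 667 | 667 | 400 |

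In the 20%/40% row the evaluable share is (1 − 0.40)/(1 − 0.20) = 0.75.

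**4. Effect on power.** Assume 50% versus 65% consistent use, two-sided 5%, 80% power and no clustering. This needs 170 evaluable women per arm.

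| d_c | d_f | Enrolled per arm | Needed per arm | Evaluable per arm | Power |
|---|---|---|---|---|---|
| 20% | 40% | 213 | 284 | 127.8 | 68% |
| 30% | 50% | 243 | 340 | 121.5 | 66% |
| 30% | 30% | 243 | 243 | 170.1 | 80% |
| 40% | 20% | 284 | 213 | 227.2 | 90% |
| 50% | 30% | 340 | 243 | 238 | 91% |

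A general approximation agrees for the first row: Φ(2.80 × √0.75 − 1.96) = 0.68.

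Clustering softens the loss, because losing women within brothels costs less than losing brothels. With an assumed ICC of 0.05 and 15 women per brothel achieved against 20 planned, the information ratio is (0.05 + 0.95/20)/(0.05 + 0.95/15) = 0.0975/0.1133 = 0.86. Power is then Φ(2.80 × √0.86 − 1.96) = 0.74.

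**The case against.** The strongest reply is that completing is undefined and has an innocent reading. The intervention lasts 16 weeks and the assessment falls at 16 weeks, so completing may simply mean still being in the brothel and the programme when the interview is due. Because adherence is listed separately as a session count, this reading is at least as natural as one based on sessions. The Study design and setting section also says that the 16-week length was chosen partly to help follow-up. In addition, no phase III number or inflation rule is fixed, and the follow-up assessments are planned, so the right rate can still be computed.

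Much of this stands, and it rules out several stronger conclusions that a reader might draw:

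- **That the two rates must diverge.** The Discussion describes delivery within a short span, "thereby enabling most of the FSWs to benefit from it before they may need to change their location". This makes it plausible that a woman receives the content and then misses the interview. It predicts nothing about how many would.
- **That a woman with fewer than six sessions who is interviewed at week 16 counts as lost.** Six sessions is a planned minimum exposure. It is not stated as a completion rule.
- **That completing is a harder test in the experimental arm.** The leader-run sessions are a delivery duty placed on the leader. Nothing makes attending them a condition of completing.
- **That phase III will be underpowered.** The error could go either way or be nil.

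The reply does not remove the core point. The article states both a measure and a data source for a primary outcome, so this is more than a detail left to a fuller document. Even on the innocent reading, presence in the programme stands in for having the outcome. The right rate could be computed, but nothing in the article says that it will be.

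**Conclusion.** The point holds as a mismatch between a stated measure and its stated use. Attrition is measured by completion of the intervention, but phase III inflation needs the proportion without a 16-week assessment, which is the sense the article itself uses when it sets the recruitment target.

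The consequence has no size or direction that the documents can supply. The power figures of 66% to 91% against a planned 80% rest wholly on assumed rates of 20% to 50%, an assumed effect and no clustering. The 74% figure adds an assumed ICC and brothel size. If the two rates coincide, nothing changes. The pilot's 59 and its target of 200 are unaffected.

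A smaller related point is that the analysis section describes attrition for the intervention arm, whereas phase III inflation needs the rate in both arms.

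**What to change.** In Measurements, replace the attrition measure with two definitions:

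- **Participant attrition:** enrolled women without a 16-week follow-up assessment, divided by all women enrolled at baseline.
- **Brothel attrition:** randomised brothels without a follow-up assessment, divided by all randomised brothels (12 if the target is met).

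In the statistical analysis section, report both for each arm and name them as the rates used to inflate the phase III sample size. Keep completion of the intervention, with an explicit definition, and report it alongside adherence.

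The cost is wording only. The baseline and follow-up assessments are already planned, so no new data are needed. The article says that the pilot is already underway, so the change should be dated and documented before the attrition data are analysed.
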